### Design

The study has a 2-arm (intervention [JU:MP] and control), quasiexperimental, nonblinded, nonequivalent group design with 3 waves of data collection (baseline [before intervention], 24 months [during intervention], and 36 months [after intervention]). Figure 3 outlines the study flow diagram.

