### Identification of Neighborhoods

The JU:MP program is operating in 8 distinct neighborhoods. The 3 neighborhoods eligible for participation in this effectiveness trial are the 3 direct-delivery neighborhoods of JU:MP. Control neighborhoods will be based on local authority wards (local areas with elected officials representing the local area) and be in the county of West Yorkshire in order to ensure that neighborhoods would be politically and geographically similar to the JU:MP neighborhoods. Other neighborhoods/wards in Bradford have been excluded due to potential intervention contamination. Control neighborhoods must ideally have similar characteristics to the JU:MP neighborhoods to maximize internal validity. The process of identifying control neighborhoods will include pooling state-funded primary school census data [33], which are released from schools annually, for every ward in West Yorkshire and then calculating the median/mean of (1) the value of the school postcode-derived IMD (IMD 2019) [34]; (2) the proportion of children eligible for state-funded free school meals (school population measure of deprivation); and (3) the proportions of the 2 predominant ethnic groups in the 3 JU:MP areas (White British and South Asian heritage [combining Pakistani heritage, Bangladesh, Indian, and other South Asian ethnic groups]). Ward areas deemed to be suitable control areas must have no more than 1 IMD decile median difference than a JU:MP neighborhood and no more than 10% difference in the proportion of children eligible for free school meals, and the predominant ethnic group (majority or large minority) must be the same as that in a JU:MP neighborhood with ideally no more than 15% difference.

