#### Child Demographics and Anthropometric Data

After the receipt of parental/carer consent, researchers will request school-stored demographic data, such as date of birth, unique pupil number (linked to health records), biological sex, ethnicity, home postcode (for IMD calculation), child’s disability or special educational needs, and receipt of government-funded free school meals, from participating schools. The immediate request is to ensure the research team can plan provisions for any children with any additional needs during testing. On the first day of data collection, the research team will ask schools to provide the most recent attendance records and educational attainment data, and a copy of the class timetable for 2 weeks starting from the date of data collection (for accelerometry data collection). Anthropometric measurements will include weight, height, BMI, and waist circumference; all will be measured by trained researchers within the school setting. Weight will be assessed barefoot and in light clothing using a digital scale (eg, Tanita body composition analyzer SC-240MA III). Height will be measured unshod, with the head placed in the correct position, on a Seca 213 stadiometer (graduation=1 mm). BMI will be calculated and converted to a BMI percentile and z-score based on UK reference data [39]. Waist circumference will be measured using a Seca 201 tape (graduation=1 mm).

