### Data Analysis

Data will be entered electronically with a double data entry protocol using REDCAP software. Data will be kept on a secure file storage system, which will also be password protected. Data will be anonymized by the assignment of a unique identification number (study ID) to each participant. The primary comparative analysis (objective 1) will be performed on an intention-to-treat basis, including all participants recruited and without imputation for missing data. Multivariable mixed effects linear regression will be used to estimate differences in the primary outcome (accelerometer-assessed mean daily minutes of moderate-to-vigorous physical activity) between the intervention and control groups. Demographic variables of gender and ethnicity will be treated as random effect variables, and baseline moderate-to-vigorous physical activity, age, accelerometer wear time, BMI z-score, school, neighborhood, and condition will be treated as fixed effect variables. Similar analyses will be repeated for secondary outcomes (objective 2). A sensitivity analysis, using a suitable imputation method, will be conducted to assess the effect of missing data. *P* values and 95% CIs will be calculated. A small number of prespecified subgroup analyses will be carried out to evaluate whether the intervention is differentially effective in different subgroups, such as by neighborhood and school (objective 3). The trial is not powered to detect effectiveness in subgroups, and this analysis will be treated as exploratory, presented using CIs, and interpreted with caution. Mediation analysis using structural equation modeling will be applied to look at whether any intervention effect is mediated by potential determinants (objective 4), including (1) home physical activity, (2) school physical activity, (3) children’s sedentary screen time behaviors, (4) travel and street physical activity, (5) parent practices (nondirective support and autonomy support), (6) neighborhood social cohesion, (7) neighborhood walking/exercise environment, (8) religious setting physical activity, (9) physical activity during sports and recreation, and (10) park/green space physical activity, which the JU:MP program could have impacted based on the complexity of the program. Multimedia Appendix 2, Multimedia Appendix 3, and Multimedia Appendix 4 present 3 directed acyclic graphs that show the simple mediating pathways to be examined, the potential causal pathways between meditating variables, and the potential casual pathways between confounders (sex, ethnicity, age, socioeconomic status, and weight status), respectively.

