As with all research, there are limitations with the proposed work detailed in this protocol. Namely, the quasiexperimental design of the work naturally has an increased risk of bias when compared with a randomized controlled trial, which is the gold standard way to detect the effects of programs and interventions [53]. However, a randomized controlled trial would not have been feasible for the JU:MP project due to the growing and developing nature of the program in preselected areas of Bradford [25]. Thus, we decided to seek to reduce the risk of bias with matching of neighborhoods based on key descriptive statistics. Another limitation of this work is the reliance on parental/carer and teacher proxy reports, which reduces the validation and reliability of the measures being taken. The reliance on proxy measures is due to the young age of the participants who will not have the capacity to accurately complete questionnaires on key health behaviors (screen time, modes of physical activity, and sleep) and secondary health outcomes such as quality of life and emotional well-being. However, the use of accelerometry as an outcome assessment overcomes the capacity issue of younger children and provides a more objective tool to measure the complex behavior of physical activity.

Many attempts have been made by researchers, practitioners, and policy makers to address children’s physical inactivity. However, previous attempts have been unsuccessful in both intervention design and the application of complex evaluations. Lack of success leads to children’s physical activity levels stagnating or worsening, increasing the risk of ill-health and negatively impacting the growth and development of young people. Sport England, the largest funder of sports and physical activity in England, has invested significant funds in 12 geographical areas in England to increase physical activity through a place-based whole-system approach. Methodologically rigorous and high-quality research is required to examine what works, why, for whom, and in what context, in order to understand the potential of whole-system approaches for increasing children’s physical activity, and whether and how they can be replicated [25]. Research evaluating one of the geographical areas (the JU:MP project in the City of Bradford) seeks to achieve this endeavor. This protocol outlines the effectiveness part of the evaluation.

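### The primary model of this non-randomized comparison has no deprivation term, although deprivation is a matching variable and is collected for every child

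*Protocol article*

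**What the plan says.** The Design section describes a "quasiexperimental, nonblinded, nonequivalent group design with 3 waves of data collection", and the Discussion accepts that "the quasiexperimental design of the work naturally has an increased risk of bias when compared with a randomized controlled trial".

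Deprivation appears in three places.

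- **Matching (Identification of Neighborhoods).** Wards are compared on "the value of the school postcode-derived IMD (IMD 2019" and on "the proportion of children eligible for state-funded free school meals (school population measure of deprivation". On the first measure, a suitable control ward "must have no more than 1 IMD decile median difference than a JU:MP neighborhood". On the second, the limit is "no more than 10% difference in the proportion of children eligible for free school meals".
- **Data collection (Child Demographics and Anthropometric Data).** For each consented child, schools are asked for the home postcode, from which IMD is to be derived, and for "receipt of government-funded free school meals".
- **Causal diagrams (end of Data Analysis).** In the sentence on the directed acyclic graphs, directly after the mediation analysis, the article names "confounders (sex, ethnicity, age, socioeconomic status, and weight status".

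The same section lists the primary model. Gender and ethnicity enter as random effects. Baseline MVPA, age, wear time, BMI z-score, school, neighborhood and condition enter as fixed effects. IMD and free school meals are not in the list, and no reason is given. The primary analysis is without imputation; an imputation-based sensitivity analysis is planned. Secondary outcomes get similar analyses.

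**The concern.** Without randomization, the protection against confounding comes from two sources: how the control areas were chosen, and what the model adjusts for. The plan treats deprivation as important enough to match on, and its Discussion says that economically deprived children are at greater risk of inactivity. The adjustment step then leaves it out, although the child-level data will be held.

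The article prints the covariates variable by variable, so this is a stated choice and not a detail left for an analysis plan. What is at stake is some avoidable bias in the condition effect at 24 and 36 months, and possibly in the secondary outcomes if the same covariates are used there.

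**Working it through.** The plan states no figure on this point, so there is none to reproduce. The check is a comparison of lists, followed by an illustrative size.

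**1. Named confounders against the listed primary model**

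| Named with the diagrams | Term in the primary model |
|---|---|
| Sex | Gender |
| Ethnicity | Ethnicity |
| Age | Age |
| Weight status | BMI z-score |
| Socioeconomic status | None |

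Four of the five have a term. Socioeconomic status is the only one without.

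**2. What matching leaves open.** Matching uses ward summaries of school census data and the school's postcode, with tolerances of 1 IMD decile and 10% on free school meals. It does not control which children consent or which supply valid accelerometer data. If the Sample Size section is read as 30% lost at baseline and then a further 50%, the analysable share is 0.70 × 0.50 = 0.35 of recruited children. Balance between ward census figures does not guarantee balance in that subset.

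**3. What baseline MVPA leaves open.** Adjusting for baseline MVPA removes part of a stable difference between deprivation groups. It does not remove deprivation-related differences in change over 24-36 months. Baseline MVPA is also measured with error: the accelerometry section gives the wear-time criterion an estimated intraclass correlation of 0.75.

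**4. Illustrative size**

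Bias ≈ (arm difference in free-school-meal share) × (MVPA difference between free-school-meal groups)

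- Arm difference: 0.10, the matching limit, read as percentage points.
- Gradient: not in the documents. Assumed 3-8 min/day.
- Before baseline adjustment: 0.10 × 3 = 0.3 and 0.10 × 8 = 0.8 min/day, which is 3-8% of the 10-minute target.
- With a wider assumed gradient of 1-10 min/day: 0.10 × 1 = 0.1 and 0.10 × 10 = 1.0 min/day.
- For IMD, with an assumed 0.2-1 min/day per decile, a 1-decile difference gives 0.2-1.0 min/day.

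*After baseline adjustment.* If the gap between groups is stable and the slope of follow-up on baseline MVPA is b, the fraction of the gradient left is 1 − b. With b assumed to be 0.4-0.6, 40-60% remains. The free-school-meal range becomes 0.3 × 0.4 = 0.12 to 0.8 × 0.6 = 0.48 min/day, about 1-5% of the target. A gap that changes over time would not shrink in this way.

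**The case against.** The strongest reply is that deprivation is already dealt with in the design. Wards are matched on two deprivation measures plus predominant ethnic group, and the Discussion names matching as the means chosen to reduce bias. The tolerances are maxima for each ward; nothing suggests that all three control areas sit at the limit in the same direction. The model also contains baseline MVPA, ethnicity and BMI z-score, each of which carries some information on deprivation. This stands, and it is why the likely bias is small. It does not make the omission harmless, for the reasons in steps 2 and 3.

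Four stronger readings are tempting but not supported.

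- **That the plan contradicts its own adjustment set.** The five-item list belongs to the diagrams for the mediation objective, and the article never calls it the covariate set for the primary analysis. The diagrams are not shown. A confounder of mediator and outcome need not confound condition and outcome. The list is supporting evidence, because the outcome is the same MVPA and the other four variables are all in the primary model.
- **That nothing in the model adjusts for deprivation.** As listed, school and neighborhood are fixed effects and would absorb deprivation differences between areas. Condition is constant within each school and neighborhood, so those terms create a separate problem of identifying its effect. The present point does not depend on how that is resolved: differences within schools are not directly adjusted for either way.
- **That imbalance among consenting children could reach, say, 30 points and bias the result by over 2 minutes.** No figure in the documents supports that imbalance, and selective consent could narrow the gap as easily as widen it.
- **That every secondary estimate is affected.** The article says only that similar analyses will be repeated and does not list their covariates.

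**Conclusion.** The point holds as a should-fix. The listed primary model of a nonequivalent-group comparison omits a child-level deprivation term that the study can supply, and matching with baseline adjustment covers only part of the gap. At the free-school-meal matching limit and an assumed gradient of 3-8 min/day, the bias is at most about 0.3-0.8 min/day before baseline adjustment and probably less after it, in unknown direction, against a 10-minute target. That would not by itself overturn a 10-minute effect. The size rests on an assumed gradient and on imbalance no larger than the ward tolerance, which the documents do not guarantee for the analysed children. The case for change rests less on the size than on a nearly free improvement to a comparison whose main weakness is confounding.

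**What to change.** Before analysis begins, add at least one baseline child-level deprivation measure as a fixed effect in the primary model: IMD 2019 from the home postcode, free-school-meal receipt, or both. Carry the same term to the similar secondary models. If the investigators prefer to leave deprivation out, they should state why.

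Say how missing values of the covariate are handled, in keeping with a primary analysis without imputation. One option is a missing category in the primary model; another is to deal with them in the imputation sensitivity analysis already planned. A missing category can leave some confounding among the children concerned, so reporting both would be sensible.

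The cost is a short addition to the analysis section and a few child-level degrees of freedom. No new data are needed. The article reports that analysis has not begun, so the change can still be prespecified; made after results are seen, it would look data-driven.

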
### Ethical Considerations

This study and all processes were given ethical approval by the University of Bradford Research Ethics Committee (Humanities, Social, and Health Sciences Research Ethics Panel; reference: E891). Informed consent will be sought from schools and parents. Children (participants) will also be asked to provide assent at every data collection timepoint. Schools in the control condition will be paid £600 (US $727) overall (£200 [US $242] for every data collection [baseline, 24-month follow-up, and 36-month follow-up]), and children will be given a “goodie bag” (includes books, stationery, and stickers) worth £2 (US $2.42) as a thank you each time they complete data collection. All data collected will be deidentified and anonymized by using ID numbers and storing all data on secure National Health Service servers, and only the principal investigator and senior researcher will have access to confidential information. All questionnaire data will be double data entered into secure databases created within RedCap.

## Results

This study has been registered at ISRCTN (ISRCTN14332797). Recruitment occurred from July 2021 to March 2022, and baseline data collection occurred from September 2021 to March 2022. As of March 2022 (end of baseline data collection), a total of 1454 children from 37 schools (17 intervention schools and 20 control schools) have been recruited. The first follow-up data collection will occur from September 2023 to March 2024, and the second and final follow-up data collection will occur from September 2024 to March 2025. Data analysis has not begun, and the final results will be published in December 2025.

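### Each wave runs from September to March, but the stated model has no date or daylight term and nothing balances visit dates between the non-randomised arms, so season can differ by arm within a wave

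*Protocol article*

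**What the plan says.** **Windows.** The Results section reports that "baseline data collection occurred from September 2021 to March 2022", that "The first follow-up data collection will occur from September 2023 to March 2024", and that "the second and final follow-up data collection will occur from September 2024 to March 2025". Each window covers seven calendar months, from early autumn through midwinter to early spring.

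**Measurement.** Under Primary Outcome Assessment: Accelerometry, each child wears the device for seven consecutive days at each timepoint.

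**Model.** Data Analysis lists the terms of the primary model. Gender and ethnicity enter as random effects. The fixed part is given thus: "baseline moderate-to-vigorous physical activity, age, accelerometer wear time, BMI z-score, school, neighborhood, and condition will be treated as fixed effect variables". Models of the same kind are planned for the secondary outcomes. The causal graphs name as "confounders (sex, ethnicity, age, socioeconomic status, and weight status" five variables, and season is not one of them.

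**Design.** The Design section describes a "quasiexperimental, nonblinded, nonequivalent group design with 3 waves of data collection". Under Identification of Neighborhoods, control wards lie in West Yorkshire but outside Bradford, and are matched on deprivation, free school meals and ethnicity. The Discussion names neighborhood matching as the means of reducing bias. No section mentions the timing of visits by arm.

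**The concern.** Children's activity plausibly depends on daylight and weather, and a seven-day record reflects the time of year in which it was taken. If one arm is measured more often in the darker part of the window, its mean moderate-to-vigorous activity is lower for a reason unrelated to the program. The comparison between arms at that wave then carries the difference as apparent effect, in either direction.

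Randomisation does not protect against this here, and none of the matching variables concerns timing. Two features make an imbalance plausible. Recruitment (July 2021 to March 2022) overlapped baseline measurement (September 2021 to March 2022), so a school recruited late could only be measured late. The arms are also geographically separate, which could make it convenient to visit them at different times. Neither feature shows that an imbalance occurred.

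The article specifies the model down to wear time and BMI z-score. If that list is followed as written, a timing imbalance stays uncorrected.

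**Working it through.** The plan states no figure on this point, so there is none to reproduce. The check has two parts: what the text fixes, and how large a bias could be.

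**1. What the text fixes**

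- Windows: September to March in all three waves, seven calendar months each. Follow-ups are at 24 and 36 months, which are whole years. At the level of the window, season is aligned across waves.
- Within a window: nothing returns a school to its baseline month. A school seen in September at baseline and in January at follow-up would fit the windows.
- Model terms: gender, ethnicity, baseline activity, age, wear time, BMI z-score, school, neighborhood and condition. None is a date, month, season or daylight term.
- Balance by arm: no statement.

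**2. Size**

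Inputs from Sample Size and Power Analysis: target 10 min, SD 19.7, ICC 0.01, three neighborhoods per arm, 1200 children, 30% data loss at baseline and a further 50% at follow-up. Assumptions, because the article gives no seasonal data: a swing of 5, 10 or 15 min/day between the lighter and darker months of the window, and a between-arm difference of 10 or 25 percentage points in the share measured in the darker months.

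Bias = difference in share × swing:

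| Imbalance | Swing 5 | Swing 10 | Swing 15 |
|---|---|---|---|
| 0 points | 0 | 0 | 0 |
| 10 points | 0.5 min | 1.0 min | 1.5 min |
| 25 points | 1.25 min | 2.5 min | 3.75 min |

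This is 5% to 37.5% of the 10-minute target when visits are unbalanced.

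For comparison with the sampling error, children analysed per neighborhood: M = (1200/6) × 0.7 × 0.5 = 70. Then

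SE = √[2 × 19.7² × (1 + 69 × 0.01) / (3 × 70)] = √(776.18 × 1.69 / 210) = √6.25 = 2.50 min.

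A bias of 2.5 min is one standard error. With a normal reference, two-sided type I error becomes 1 − Φ(1.96 − 1) + Φ(−1.96 − 1) = 17% instead of 5%. With a noncentral t on 4 degrees of freedom (six neighborhoods minus two) and noncentrality 1, it is about 12%. At 0.5 min it is about 5.5% (normal) or 5.3% (t).

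**3. What baseline adjustment does**

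With slope b on baseline activity, net bias ≈ bias at follow-up − b × bias at baseline. If each school keeps its calendar month, a 2.5-min imbalance is present at both waves. For an assumed b of 0.3 to 0.7, what remains is 2.5 × (1 − 0.3) = 1.75 to 2.5 × (1 − 0.7) = 0.75 min. Adjustment removes part of a stable imbalance and does not remove one that arises only at follow-up.

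**The case against.** The strongest reply is that the plan already handles season. The windows are identical, the intervals are whole years, and the controls are measured concurrently. A seasonal shift shared by both arms cancels in a between-arm contrast, and baseline activity absorbs part of an imbalance that persists. This stands, and it rules out a reading that a reader might otherwise make: that season is systematically confounded with wave. What remains is imbalance by arm inside a window.

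Other inferences also go beyond the text:

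- **That each school is measured in a single week, or that arms are visited in blocks.** The article says neither. It gives seven days of wear per child and no visit dates. The Recruitment of Schools section ties the number of control schools, not their timing, to intervention recruitment.
- **That a difference in mean measurement date converts at a fixed number of minutes per month.** Daylight falls and then rises within the window, so two arms with equal mean dates can still differ in season, and arms with different mean dates can match. The share measured in the darker months is the better measure.
- **That season inflates between-school variance.** In the stated model school is a fixed effect and would absorb such differences.

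It can also be said that visit scheduling belongs in the full protocol and that a seasonal term may sit in an analysis plan not shown; the timescale and flow figures are also not shown. That is fair for scheduling and keeps the point modest. It is weaker for the model, because the article does set out a covariate list without a seasonal term.

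**Conclusion.** The point holds in a limited form. A seven-month window, one wear period per wave, non-randomised arms in different places and a stated model with no seasonal term together leave the between-arm contrast open to a timing imbalance. The documents do not show that an imbalance exists.

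Under the assumed swing and imbalances above, the bias is about 0.5 to 3.75 min against a target of 10, and zero if visits are balanced by arm. At the lower end it is minor. At the upper end it exceeds the approximate standard error of 2.50 min. The range rests wholly on assumed inputs and should be replaced once baseline dates are tabulated. The value of acting is that it is cheap, and that the timing of a follow-up visit cannot be changed after the visit.

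**What to change.** 1. Tabulate baseline measurement dates by arm, by month or by daylight hours. The information should already exist in the accelerometer records. It shows whether there is a problem at baseline.
2. At 24 and 36 months, revisit each school near its baseline calendar week and, as far as that allows, interleave intervention and control schools within each month. If baseline visits turn out to have been clustered by arm, the two aims conflict, and the choice between them should be recorded in advance.
3. Prespecify daylight hours (or month) in the measurement week, at follow-up and at baseline, as covariates in the primary and the secondary accelerometer models. School must then be a random rather than a fixed effect. The plan states that "BMI z-score, school, neighborhood, and condition will be treated as fixed effect variables", and a date that varies only between schools cannot be estimated alongside school fixed effects. With school random, the term can be estimated across the 37 schools. The school term needs attention in any case, because each school lies in one arm and school fixed effects also absorb condition.

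The article places both follow-ups ahead and says that analysis has not begun. If a wave has since been completed, steps 1 and 3 still apply to it.

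Cost: some scheduling constraint within a window already planned, one or two extra model terms derived from measurement dates, and the need to reconcile the school term first.
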